## Abstract

**Background:**

Ischemic brain injury is a major hurdle that limits the survival of resuscitated out-of-hospital cardiac arrest (OHCA).

**Methods:**

The aim of this study is to assess the feasibility and potential for reduction of ischemic brain injury in adult OHCA patients treated with high- or low-dose Neu2000K, a selective blocker of *N*-methyl-d-aspartate (NMDA) type 2B receptor and also a free radical scavenger, or given placebo. This study is a phase II, multicenter, randomized, double-blinded, prospective, intention-to-treat, placebo-controlled, three-armed, safety and efficacy clinical trial. This trial is a sponsor-initiated trial supported by GNT Pharma. Successfully resuscitated OHCA patients aged 19 to 80 years would be included. The primary outcome is blood neuron-specific enolase (NSE) level on the 3rd day. The secondary outcomes are safety, efficacy defined by study drug administration within 4 h in > 90% of participants, daily NSE up to 5th day, blood S100beta, brain MRI apparent diffusion coefficient imaging, cerebral performance category (CPC), and Modified Rankin Scale (mRS) at 5th, 14th, and 90th days. Assuming NSE of 42 ± 80 and 80 ± 80 μg/L in the treatment (high- and low-dose Neu2000K) and control arms with 80% power, a type 1 error rate of 5%, and a 28% of withdrawal prior to the endpoint, the required sample size is 150 patients.

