### Sample size {14}

The primary hypothesis of this trial is that patients receiving Neu2000K will have lower blood NSE levels on the 3rd day compared with those receiving placebo. Based on a prior study, the NSE level on the 3rd day of the control group was estimated to be about a mean of 90 μg/L and a standard deviation of 80 μg/L [31]. We assumed that any dose group compared to the placebo group can lower the NSE level on the 3rd day to 40 μg/L or less. Consequently, a total of 150 patients (50 per arm) are needed for this trial with the consideration of power of 84%, one-sided alpha of 0.05, and dropout rates of 28%.

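### The abstract and the sample-size section justify the same 150 patients with different planning means and power, and the abstract's figures do not give its stated 80% power

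*Protocol article*

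**What the plan says.** The Methods paragraph of the abstract plans on mean NSE of 42 μg/L under treatment and 80 μg/L under control, with an SD of 80 μg/L for each. It gives these values "in the treatment (high- and low-dose Neu2000K) and control arms with 80% power, a type 1 error rate of 5" per cent, and does not say whether that level is one- or two-sided. Allowing for 28% loss before the endpoint, it arrives at 150 patients.

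Section Sample size {14} puts control at "about a mean of 90 μg/L and a standard deviation of 80 μg/L", citing a prior study. It then assumes that "any dose group compared to the placebo group can lower the NSE level on the 3rd day to 40 μg/L or less". Its conclusion is 150 in total, split equally at 50 for each arm; these, it says, "are needed for this trial with the consideration of power of 84%, one-sided alpha of 0.05, and dropout rates of 28" per cent.

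Section Statistical methods {20a} sets the primary test as a t-test or Mann–Whitney test at a one-sided 5% level. Section {20b} says that no adjustment is made for multiple tests.

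**The concern.** The two statements agree on SD (80 μg/L), loss (28%) and total (150). They differ on both means, on the difference to be detected and on the power. Rounding does not turn 90 into 80 or 84% into 80%. A smaller difference at the same SD, level and evaluable number lowers power far more than four percentage points, so both statements are unlikely to be right.

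This matters for reading the result. Stated power tells the reader how much weight a null finding on the primary endpoint can bear. If 38 μg/L is the real expectation, the chance of missing a given working dose is about 36% (1 − 0.637) and not the 20% that the abstract implies. The discussion section looks ahead to a phase III trial, so a null result could be over-read.

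**Working it through.** **Inputs**

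| | Abstract | Sample size {14} |
|---|---|---|
| Control mean (μg/L) | 80 | 90 |
| Treated mean (μg/L) | 42 | 40 (or less) |
| Difference (μg/L) | 38 | 50 |
| SD (μg/L) | 80 | 80 |
| Standardised difference d | 38/80 = 0.475 | 50/80 = 0.625 |
| Power | 80% | 84% |
| Type 1 error | 5%, side not given | 5%, one-sided |
| Loss | 28% | 28% |
| Total | 150 | 150 (50 per arm) |

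Allocation is 1:1:1, so the evaluable number is 50 × 0.72 = 36 per arm.

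**Formula.** With n₀ evaluable on placebo and n₁ on active treatment, approximate power is Φ(d/√(1/n₀ + 1/n₁) − z), with z = 1.645 for one-sided 5% and 1.960 for two-sided 5%. Exact t-test power comes from the noncentral t distribution.

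**Step 1: reproduce Sample size {14}.** One dose against placebo, 36 and 36: 0.625/√(2/36) = 2.652, and 2.652 − 1.645 = 1.007, so power is 84.3% (t-test 83.7%). This agrees with the stated 84%. In reverse, 84% power needs 36 evaluable per arm; 36/0.72 = 50 per arm, 150 in total. The stated power is therefore that of one unadjusted, one-sided comparison of a single dose with placebo.

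**Step 2: the abstract's figures, same evaluable numbers.**
- One dose against placebo, 36 and 36: 0.475/√(2/36) = 2.015. One-sided: 2.015 − 1.645 = 0.370.
- Both doses pooled against placebo, 72 and 36: 0.475/√(1/36 + 1/72) = 2.327. One-sided: 2.327 − 1.645 = 0.682.

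| Comparison | Side | Normal approx. | t-test |
|---|---|---|---|
| One dose vs placebo | one | 64.4% | 63.7% |
| One dose vs placebo | two | 52.2% | 51.1% |
| Pooled vs placebo | one | 75.2% | 74.8% |
| Pooled vs placebo | two | 64.3% | 63.5% |

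None reaches 80%.

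**Step 3: total needed for 80% on the abstract's figures (t-test).** Divide the evaluable number per arm by 0.72, round up, multiply by three.

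| Comparison | Side | Evaluable per arm | Enrolled per arm | Total |
|---|---|---|---|---|
| One dose vs placebo | one | 56 | 78 | 234 |
| One dose vs placebo | two | 71 | 99 | 297 |
| Pooled vs placebo | one | 42 | 59 | 177 |
| Pooled vs placebo | two | 53 | 74 | 222 |

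The normal approximation gives 231 and 294 for the single-dose rows, which does not change the conclusion.

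**Step 4: could the loss allowance explain it?** With no loss at all (50 per arm), one dose against placebo reaches 76.2% one-sided. The pooled comparison reaches 86.1% one-sided, but only by ignoring the 28% loss that the abstract itself includes.

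**The case against.** The strongest reply is that a third criterion gives 80%. The abstract assigns 42 μg/L to both doses, the sample-size section speaks of any dose group, and no multiplicity adjustment is planned. The probability that at least one dose is significant, each tested one-sided at an unadjusted 5% with 36 evaluable per arm, is 79.9% on the abstract's figures. That is 80% after rounding.

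This does not rescue the statement. The document nowhere states the criterion. It carries a familywise error of about 8.8%, whereas the abstract claims 5%; with a Dunnett adjustment to 5% the probability drops to 70.5%. On the values of Sample size {14} the same criterion gives 93.8% and not 84%, so the two statements still could not both be right. What stands is that the shortfall must be tied to a criterion: it holds for a dose tested singly and for the doses pooled.

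Three further points on that side are fair. The sample-size section is the designated place for the calculation, cites a prior study for its control values and reproduces, so a slip in the abstract is the likelier explanation and an underpowered design the less likely one. The one-in-three risk of a miss applies only if 38 μg/L is what the sponsor expects. The two-sided figures carry little weight, because the body of the article fixes a one-sided test. None of this removes the contradiction, and nothing in the article tells the reader which set of values was the planned one.

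**Conclusion.** The concern holds. The article gives two incompatible sets of planning values for the primary endpoint, and only that of Sample size {14} supports 150 patients at its stated power (83.7% against 84%). On the abstract's figures, one-sided power is about 64% for one dose against placebo and about 75% for the doses pooled, against a stated 80%.

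These results assume 36 evaluable per arm after 28% loss, a common SD of 80 μg/L, a t-test and no multiplicity adjustment. They do not show that the trial is underpowered; that depends on which difference the sponsor expects. They do show that the abstract's power statement is wrong as written for both comparisons.

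**What to change.** Keep 150 patients and use one set of planning values everywhere.

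- **Preferred:** replace the abstract's figures with those of Sample size {14}: 90 against 40 μg/L, SD 80, one-sided 5%, 84% power, 28% loss, 150 patients.
- **If 42 against 80 μg/L is the true expectation:** carry those values into Sample size {14} as well, and restate the one-sided power as about 64% per dose (about 75% pooled).

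In either case, state that the power refers to a single unadjusted comparison of one dose with placebo, which is the calculation that reproduces.

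The cost is wording only, with no added patients and no change to the design or the primary test. Under the second option a less favourable power has to be reported.

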**Discussion:**

The AWAKE trial explores a new multi-target neuroprotectant for the treatment of resuscitated OHCA patients.

**Trial registration:**

ClinicalTrials.gov NCT03651557. Registered on August 29, 2018.

## Administrative information

The items of checklist for clinical trial protocol recommended by Standard Protocol Items: Recommendations for Interventional Trials (SPIRIT) 2013 statement are indicated by braces (http://www.equator-network.org/reporting-guidelines/spirit-2013-statement-defining-standard-protocol-items-for-clinical-trials/).

Note: the numbers in curly brackets in this protocol refer to SPIRIT checklist item numbers. The order of the items has been modified to group similar items (see http://www.equator-network.org/reporting-guidelines/spirit-2013-statement-defining-standard-protocol-items-for-clinical-trials/).

## Introduction

### Background and rationale {6a}

Out-of-hospital cardiac arrest (OHCA) is a major public health challenge. The global incidence of OHCA ranges from 20 to 140 per 100,000 person-years, with low short-term survival rates from 2 to 16% [1–4]. Global brain ischemia and reperfusion are the key pathophysiology underlying OHCA. Manual chest compression attempts during resuscitation typically provide only 15 to 25% of normal cardiac output [5]. Impaired cerebral perfusion does not allow the delivery of vital materials such as oxygen and glucose, leading to the depletion of metabolic energy. In addition, full restoration of cerebral perfusion is not completely harmless and causes additional reperfusion injuries [6].

Excitotoxicity is one of the major pathogenic mechanisms underlying ischemic and reperfusion brain injury [7]. It is predominantly triggered by the overactivation of *N*-methyl-d-aspartate (NMDA) receptors and followed by extracellular calcium influx, loss of cell membrane potential, oxidative stress, and eventually, neuronal death [8, 9]. Toxic free radicals such as superoxide and hydrogen peroxide are produced and accumulated in the neurons and glia through mechanisms involving reoxygenation and iron overload during reperfusion as well as intracellular calcium overload subsequent to the activation of NMDA receptors, which triggers delayed neuronal and glial cell death [10, 11].

Given the pivotal role of NMDA receptors in excitotoxicity, NMDA receptor antagonists have been considered as one of the promising therapeutic targets for neuroprotection against ischemic and reperfusion neuronal injury [12]. However, despite the initial encouraging results in preclinical studies, prior NMDA receptor blockers have failed to be translated for clinical use [13, 14]. The explanation for these failures of translation is likely to be multifactorial. The blockade of excitotoxicity prevents rapidly evolving neuronal death after hypoxic-ischemic brain injury; however, it delays neuronal apoptosis through mechanisms involving intracellular Ca^2+^ ion deficiency and caspase-3 activation [7, 15–19]. The clinical use of NMDA receptor antagonists is also limited by the short therapeutic time window and adverse effects such as nausea, vomiting, cardiovascular and psychomimetic effects, and oxidative stress that causes delayed brain damage after ischemic reperfusion injury [20–22].

These therapeutic boundaries may be overcome by understanding the pathophysiology first and then improving the therapeutic strategies subsequently. Targeted temperature management, which significantly reduces excitatory amino acid neurotransmitters that activate NMDA receptors, has been widely performed for post-resuscitation care of OHCA [23–25]. NMDA receptor has dual roles in neuronal survival and death. The stimulation of extrasynaptic NMDA receptors is associated with pro-death pathways, whereas the stimulation of synaptic NMDA receptors activates pro-survival signaling pathways and enhances the intrinsic antioxidant system [26, 27]. Therefore, selective NMDA receptor blockade focusing on the neuroprotective role without causing excessive reduction of calcium influx and boosting the antioxidative defenses is expected to improve the neurological outcome of OHCA [7, 11, 18, 19].

Neu2000 (nelonemdaz, an international nonproprietary name, 2-hydroxy-5-[2,3,5,6-tetrafluoro-4-trifluoromethyl-benzylamino)-benzoic acid]) is a novel, multi-target neuroprotective agent. Neu2000 was designed to prevent NMDA receptor-mediated excitotoxicity by moderately and selectively inhibiting the NR2B subtype of the NMDA receptor and also to block oxidative stress as a potent free radical scavenger. It remarkably attenuates neuronal death, oxidative stress, and infarct after ischemic-reperfusion brain injury in animal models; however, it does not cause neurotoxicity unlike the other potent NMDA receptor antagonists (Fig. 1) [22]. Compared to NMDA antagonists or antioxidants alone, the administration of Neu2000 showed better neuroprotection and a longer therapeutic window [22, 28–30]. In two phase I studies of Neu2000K (Neu2000 potassium salt) for 165 healthy subjects conducted in the USA and China, the intravenous administration of even 6000 mg Neu2000K did not produce serious adverse events such as psychosis [11]. Two phase II studies of Neu2000K for acute ischemic stroke patients receiving recanalization therapy have been completed (NCT04486430, NCT02831088). Based upon promising safety and efficacy profiles in preclinical and clinical studies, a phase III study of Neu2000K has been initiated for acute ischemic stroke patients receiving endovascular thrombectomy (NCT05041010).

**Fig. 1 Fig1:**
[figure not shown]
Mechanism of Neu2000K as a dual-target neuroprotectant for ischemic and reperfusion brain injury. In patients suffering from cardiac arrest, oxygen and glucose are deprived from the brain, which results in glutamate release and accumulation at the synaptic cleft. Excess glutamate causes acute and fulminant neuronal death through the overactivation of calcium ion-permeable NMDA receptors. Free radicals such as superoxide and hydrogen peroxide are produced in the mitochondria over hours and days after the return of spontaneous circulation. Such prolonged and excessive oxidative stress causes delayed cell death including the neurons and glia. Neu2000K moderately and selectively blocks the NR2B subtype of NMDA receptor, which activates pro-survival signaling pathways without causing excessive calcium influx, which can reduce acute neuronal death. Neu2000K also functions as a potent reactive oxygen species scavenger and reduces oxidative stress or reperfusion injury, which can reduce delayed brain cell death

The present trial will investigate the neuroprotective capabilities of Neu2000K for patients resuscitated from OHCA and undergoing targeted temperature management.

### Objectives {7}

The primary objective of this trial is to evaluate the feasibility and potential for reduction of ischemic brain injury in adult OHCA patients treated with high- or low-dose Neu2000K, and the second objective is to evaluate the safety of intravenous administration of Neu2000K in adult OHCA patients.

### Trial design {8}

The Antioxidant and NMDA receptor blocker Weans Anoxic brain damage of KorEa OHCA patients (AWAKE) trial is a sponsor-initiated, randomized, placebo-controlled, double-blinded, prospective, intention-to-treat, three-armed, safety and efficacy clinical phase II trial.

## Methods: participants, interventions, and outcomes

### Study setting {9}

Patients will be enrolled in the following tertiary university hospitals offering highly specialized cardiac care in Korea: Samsung Medical Center, Chonnam National University Hospital, Pusan National University Hospital, Gangnam Severance Hospital, and Soonchunhyang University Bucheon Hospital.

GNT Pharma and the Ministry of Health and Welfare of the Republic of Korea are sponsors of this trial. The trial will be conducted with the help of a clinical research organization, Medical Excellence based in Seoul. The authors are solely responsible for the design and conduct of this study, all study analyses, the drafting and editing of the paper, and its final contents.

### Eligibility criteria {10}

#### Inclusion criteria

Adult patients aged 19–80 years, with a witnessed OHCA, successful resuscitation defined by the sustained return of spontaneous circulation (ROSC) time ≥ 20 min, and planned or initiated targeted temperature management (32–34 C for 24 h), are eligible for inclusion in this study. These criteria are designed to identify patients with presumed cardiac causes. Intravenous administration of the investigational drug in these patients should be feasible within 4 h after ROSC.

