#### Exclusion criteria

The following are the exclusion criteria: unwitnessed arrest, resuscitation time ≥ 60 min, no indication for targeted temperature management, simultaneous application of ECMO during resuscitation, respiratory arrest without concomitant or ensuing cardiac arrest, suspected or confirmed intracranial hemorrhage, major stroke, significant baseline neurological disease, arrest subsequent to traumatic injury or major bleeding, end-stage malignancy or non-cardiac organ dysfunction, very poor expected neurological or medical prognosis, no confirmed absence of pregnancy in a potentially fertile woman, and hypersensitivity to aspirin or sulfasalazine. Exclusion criteria are considered only if they are known before the start of treatment.

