### Intervention description {11a}

#### Neu2000K high-dose group

The 1st infusion of 1500 mg within 4 h after OHCA onset, followed by 5 consecutive infusions of 750 mg at intervals of 12 h. The total dosage is 5250 mg.

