#### Neu2000K low-dose group

The 1st infusion of 750 mg within 4 h after OHCA onset, followed by 5 consecutive infusions of 500 mg at intervals of 12 h. The total dosage is 3250 mg.

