#### Placebo group

The 1st infusion of the same volume of saline within 4 h after OHCA onset, followed by 5 consecutive infusions of the same volume of saline at intervals of 12 h.

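### The 4 h limit on the first infusion runs from ROSC in the eligibility criteria but from arrest onset in all three arms, and the abstract's > 90% timeliness criterion names no start point

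*Protocol article*

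**What the plan says.** The article gives the 4 h limit in five places, with two different origins and one that is unstated.

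- Eligibility criteria {10}, Inclusion criteria, counts from ROSC: "Intravenous administration of the investigational drug in these patients should be feasible within 4 h after ROSC".
- Intervention description {11a}, high-dose group, counts from onset: "The 1st infusion of 1500 mg within 4 h after OHCA onset".
- Low-dose group, also from onset: "The 1st infusion of 750 mg within 4 h after OHCA onset".
- Placebo group, also from onset: "The 1st infusion of the same volume of saline within 4 h after OHCA onset".
- Abstract, Methods, lists among the secondary outcomes: "efficacy defined by study drug administration within 4 h in > 90% of participants". No origin is given.

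Two further places bear on the point. The exclusion criteria remove patients with "resuscitation time ≥ 60 min", the only stated limit related to the gap between the two origins. Outcomes {12} lists the primary and secondary endpoints and does not include the > 90% criterion.

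**The concern.** Onset and ROSC are different events. Because the arrest must be witnessed, both can be timed, so these are two workable clocks and not two names for one. The onset wording stands in every arm, which makes an isolated slip unlikely.

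Two things depend on the answer. The first is deviations: the section on protocol amendments {25} requires every deviation to be documented on a breach report form, and whether a late first infusion is one depends on which section is read. The second is the > 90% criterion, the only numerical target for timely delivery in the article. It cannot be evaluated until its start point is named. Its efficacy label and its absence from Outcomes {12} add doubt about what it is and whether it will be reported.

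**Working it through.** The plan derives no figure on this point, so there is none to reproduce. The check is a comparison of the two limits and an illustration of what the choice does to the > 90% criterion.

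**1. Relation between the limits.** Let t be minutes from onset to ROSC and d minutes from ROSC to first infusion.

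- ROSC limit: d ≤ 240.
- Onset limit: t + d ≤ 240, that is d ≤ 240 − t.

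Since t > 0, meeting the onset limit implies meeting the ROSC limit. Conflict arises only when 240 − t < d ≤ 240.

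| t (min) | Time left after ROSC on the onset clock (min) |
|---|---|
| 10 | 240 − 10 = 230 |
| 30 | 240 − 30 = 210 |
| 50 | 240 − 50 = 190 |
| 59 | 240 − 59 = 181 |

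Example: t = 50, d = 210. ROSC clock: 210 ≤ 240, met. Onset clock: 50 + 210 = 260 > 240, missed by 20 min.

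**2. How large t can be.** Resuscitation times of 60 min or more are excluded. The article does not define resuscitation time as onset to ROSC. If it starts when resuscitation begins, any earlier delay is added, so 60 min is a guide to t and not a strict cap.

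**3. Effect on the > 90% criterion.** The article gives no dosing times, so these are assumptions: t uniform on 5 to 59 min; d normal with SD 40 min and mean m; t and d independent.

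- Share within 4 h of ROSC = Φ((240 − m)/40).
- Share within 4 h of onset = average of Φ((240 − t − m)/40) over t from 5 to 59.

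Simulation with one million draws gives:

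| m (min) | From ROSC | From onset | Against > 90% |
|---|---|---|---|
| 150 | 98.8% | 91.2% | passes on both |
| 170 | 96.0% | 81.1% | verdict changes |
| 180 | 93.3% | 74.2% | verdict changes |
| 190 | 89.5% | 66.2% | fails on both |

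For example, at m = 170 the first formula gives Φ(70/40) = Φ(1.75) = 96.0%. Evaluating both formulas exactly agrees with every entry to within 0.1 percentage point.

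**4. What does not move.** The primary endpoint is day-3 NSE. Section {20a} defines the analysis populations by eligibility, consent, randomisation and a completed day-3 NSE test. Section {20c} defines the per-protocol set by the number of infusions received. Sample size {14} uses NSE means, an SD, alpha, power and dropout. None of these uses the time of the first infusion.

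**The case against.** The strongest reply is that little of the trial's inference rests on the clock. The infusion at 260 min in the example removes nobody from the intention-to-treat, full or per-protocol set as defined. Randomisation is blocked within site, so even if sites did read the limit differently, this would be balanced across arms. All of that stands, and it confines the point to conduct, deviation classification and one secondary criterion.

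Several stronger readings are tempting and are not supported:

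- A reader might infer that the primary objective is undermined, because Objectives {7} includes feasibility. The abstract lists the criterion as a secondary outcome and calls it efficacy; no section says that it operationalises feasibility. The link is plausible from its content but remains an inference.
- A reader might infer that the gap is at most 60 min, or 25% of the window. The exclusion criterion does not establish that cap.
- A reader might infer that the clock always decides the > 90% result. The table shows cases where it does not.
- A reader might infer that patients are preselected to satisfy the criterion. Eligibility asks whether timely dosing is expected to be possible; the criterion concerns what was actually given, and a patient judged feasible can still be dosed late.
- A reader might infer that sites are using different clocks. The article shows no such divergence, and section {11c} describes study-specific training and a study flow sheet.

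What the reply does not remove is the contradiction itself. Nothing in the article equates the two origins or ranks them.

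**Conclusion.** The point holds in limited form. The eligibility section and the three arm descriptions set different limits under the same 4 h figure, so a patient can be eligible, be dosed as eligibility foresees, and still fall outside the arm description. The discordant period equals the onset-to-ROSC interval: 30 min for ROSC at 30 min, 59 min for ROSC at 59 min. That part rests on the text alone.

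The > 90% criterion has no determinate meaning as written. Whether this changes its result depends on dosing times that the article does not give. Under the stated assumptions, the verdict changes at mean ROSC-to-drug times of 170 and 180 min, but not at 150 or 190 min.

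This is an internal inconsistency that needs correcting. It is more than clerical, because it changes who counts as a dosing deviation and may change whether a stated criterion is met. It is no threat to the day-3 NSE comparison, the analysis sets or the sample size.

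**What to change.** 1. Reconcile the inclusion criteria with the three arm descriptions so that the 4 h limit has one start point throughout. Which one is a clinical decision for the sponsor and investigators.
2. Name that start point in the > 90% criterion, describe it as a measure of delivery or feasibility instead of efficacy, and list it in Outcomes {12}.
3. Report time to first infusion from both onset and ROSC, so that patients already enrolled can be classified either way.

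The cost is a clarifying amendment. Trial status records 89 of the planned 150 patients recruited, with recruitment continuing, so some enrolled patients may be reclassified as dosing deviations. Sample size and primary analysis need no change.
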